## Abstract

**Background:**

America’s increasing HIV epidemic among youth suggests the need to identify novel strategies to leverage services and settings where youth at high risk (YAHR) for HIV can be engaged in prevention. Scalable, efficacious, and cost-effective strategies are needed, which support youth during developmental transitions when risks arise. Evidence-based behavioral interventions (EBIs) have typically relied on time-limited, scripted, and manualized protocols that were often delivered with low fidelity and lacked evidence for effectiveness.

**Objective:**

This study aims to examine efficacy, implementation, and cost-effectiveness of easily mountable and adaptable, technology-based behavioral interventions in the context of an enhanced standard of care and study assessments that implement the guidelines of Centers for Disease Control and Prevention (CDC) for routine, repeat HIV, and sexually transmitted infection (STI) testing for high-risk youth.

**Methods:**

Youth aged between 12 and 24 years (n=1500) are being recruited from community-based organizations and clinics serving gay, bisexual, and transgender youth, homeless youth, and postincarcerated youth, with eligibility algorithms weighting African American and Latino youth to reflect disparities in HIV incidence. At baseline and 4-month intervals over 24 months (12 months for lower-risk youth), interviewers monitor uptake of HIV prevention continuum steps (linkage to health care, use of pre- or postexposure prophylaxis, condoms, and prevention services) and secondary outcomes of substance use, mental health, and housing security. Assessments include rapid diagnostic tests for HIV, STIs, drugs, and alcohol. The study is powered to detect modest intervention effects among gay or bisexual male and transgender youth with 70% retention.

Youth are randomized to 4 conditions: (1) enhanced standard of care of automated text-messaging and monitoring (AMM) and repeat HIV/STI testing assessment procedures (n=690); (2) online group peer support via private social media plus AMM (n=270); (3) coaching that is strengths-based, youth-centered, unscripted, based on common practice elements of EBI, available over 24 months, and delivered by near-peer paraprofessionals via text, phone, and in-person, plus AMM (n=270); and (4) online group peer support plus coaching and AMM (n=270).

**Results:**

The project was funded in September 2016 and enrollment began in May 2017. Enrollment will be completed between June and August 2019. Data analysis is currently underway, and the first results are expected to be submitted for publication in 2019.

**Conclusions:**

This hybrid implementation-effectiveness study examines alternative models for implementing the CDC guidelines for routine HIV/STI testing for YAHR of acquiring HIV and for delivering evidence-based behavioral intervention content in modular elements instead of scripted manuals and available over 24 months of follow-up, while also monitoring implementation, costs, and effectiveness. The greatest impacts are expected for coaching, whereas online group peer support is expected to have lower impact but may be more cost-effective.

**Trial Registration:**

ClinicalTrials.gov NCT03134833; https://clinicaltrials.gov/ct2/show/NCT03134833 (Archived by WebCite at http://www.webcitation.org/76el0Viw9)

**International Registered Report Identifier (IRRID):**

DERR1-10.2196/11165

## Introduction

### Background

America’s HIV epidemic among youth aged 12 to 24 years has significantly increased in the last 15 years [1,2]. Young people now represent 26% of the HIV epidemic [1,2] despite investments in evidence-based behavioral interventions (EBI) and more recent scale-up of innovative antiretroviral treatments that can stop acquisition of HIV, which are known as preexposure prophylaxis (PrEP) and postexposure prophylaxis (PEP) [3,4]. Adolescents continue to become infected at disproportional rates [4]. It is critical to intervene with youth at high risk (YAHR) of acquiring HIV before they become infected. This study aims to intervene with YAHR with a set of interventions, which could be easily mounted, tailored, adapted over time, and broadly disseminated.

YAHR are those in urban epicenters and increasingly in the southeastern United States, particularly men who have sex with men (MSM) and transgender youth [1]. Homeless youth are also at elevated HIV risk, yet the last HIV seroprevalence study was conducted in 1991, showing 5.3% prevalence [5]. Youth in the criminal justice system may also be at elevated HIV risk [6,7]. YAHR are difficult to identify and intervene with in medical clinics because most youth (about 60% of general adolescent population) do not access health care [8-10]. Adolescents typically fail to disclose their sexual behaviors to their families or their physicians, most often because they are never asked about risk [11-13]. YAHR are likely to be encountered at agencies serving lesbian, gay, bisexual, transgender, and queer (LGBTQ) youth; homeless shelters; in the criminal justice system; and through in-person or Web spaces associated with sexual networking [14]. In each geographic epicenter of HIV, African American and Latino youth are at the highest relative risk of contracting HIV [1,15]. YAHR also typically seek peers, economic opportunities, and social services in the neighborhoods associated with the highest prevalence of HIV such as Hollywood in Los Angeles and the French Quarter in New Orleans [16]. This study uses community-based recruitment and screening to identify YAHR (see details in Rotheram-Borus et al [17]).

The current paradigm for reaching global HIV prevention goals (ie, increased uptake of the HIV prevention continuum [18]) is far more complex today than it was in the first 25 years of the epidemic. The US Centers for Disease Control and Prevention (CDC) recommends repeat and routine testing for HIV and sexually transmitted infection (STI) for YAHR every 3 or 6 months, as well as concurrently linking youth to HIV prevention and health care services and retaining them in care over time [19]. This study aims to operationalize and evaluate the impact of these guidelines using community-based recruitment and implementation of rapid diagnostic testing, referral and linkage to services, and easily scalable and tailorable technology-mediated interventions. The possibility now exists to implement biomedical and combination biobehavioral prevention for YAHR, which requires that youth know their serostatus (ie, be repeatedly tested for HIV over time), be linked to medical care, and consistently adhere to a strategy to protect themselves from HIV (eg, high adherence to PrEP, PEP, and condom use [18]). Textbox 1 summarizes the multiple endpoints for operationalizing uptake of HIV prevention continuum. These are particularly challenging tasks because the developmental challenges of youth evolve with age and may be more difficult for gay, bisexual, and transgender youth; homeless youth; and youth involved in criminal justice because of discrimination and stigma, which are often exacerbated for African American and Latino youth [11,20-23].

The HIV prevention continuum for seronegative high-risk youth.Test negative for HIVReceive health care twice annuallyAdherence consistently to prevention optionsPreexposure prophylaxis orPostexposure prophylaxis after condomless sexual encounters orCondom useRepeat HIV and sexually transmitted infection testing 3 times annually

### A New Model for Intervention Design and Delivery

Traditional EBIs for HIV prevention rely on highly scripted and manualized protocols, delivered in-person, and that are time limited and became increasingly brief in numbers of and durations of sessions over the past 20 years [24]. Although EBIs for youth HIV prevention have been selected and diffused by the CDC on the basis of demonstrated efficacy in trials, they have been challenging to scale up and lack evidence for effectiveness [24]. These EBIs are highly structured and scripted manual-based protocols, which have been noted as being difficult to implement with fidelity and are not tailorable to intervention facilitators’ and youths’ varying styles, preferences, hierarchies of needs, development stages, and HIV risks. They also typically rely on in-person visits at community-based organizations (CBOs) or health care settings. Disruptive innovations of massively scalable mobile and social media technologies may be able to implement and broadly reach youth with prevention messages and linkage to services [24-26]. Bower and Christensen [27] defined the concept of disruptive innovations in *Harvard Business Review* as simpler, cheaper, and *good enough* solutions to meet the majority of consumers’ needs and preferences relative to incumbent products and services that are often designed for the highest-need consumers, for example, ATM machines versus bank tellers, US $2 reading glasses versus specialized prescriptions, or minute clinics in pharmacies. Rotheram et al (2012) applied this concept to EBIs for youth behavioral and mental health problems by positing that interventions based on common practice elements identified across manualized EBIs, and technology-mediated modalities could be disruptive innovations that might be more scalable, adaptable, and amenable to providers’ and patients’ needs and preferences [24].

Advances in mobile phone and social media technologies have created opportunities to engage and intervene with large numbers of youth at relatively low costs, using technologies that permeate their daily routines [25,28]. This study will use 2 primary technology platforms, that is, text messaging and social media, in addition to telephone and in-person visits based on youths’ preferences. Text messaging, email, and social media use are nearly universal among youth [29-31]. Approximately 90% of youth report having a mobile phone [31-33], 90% of them text about 30 times each day [31]; rates are similar for homeless youth but with some inconsistency in maintaining service [29,30,34]. Similarly, over 90% of youth access the Web daily, and smartphones have become the primary mode of accessing the internet for the majority of youth [31].

This study’s automated and interpersonally delivered technology-mediated interventions are based on the shared features of existing EBI—we do not aim to create a new smartphone app or an EBI with a manual to be *replicated with fidelity* [35,36]. In the last 25 years, over 100 HIV EBIs and 36 adolescent sexual health EBIs have been identified by the CDC and other review bodies as efficacious [37-39] and supported for diffusion. Members of this study team rated the manuals of 5 of the CDC’s most popular, behaviorally oriented primary prevention EBIs for adolescents [36,40,41,42], finding that each of them incorporated common processes, principles, and factors. Each of the EBIs are also based on cognitive behavioral theories, even though some researchers cited a more specific iteration (eg, social cognitive theory, theory of reasoned action, and the AIDS risk reduction model) or meta-theory (eg, information-motivation-behavior and social action theory). The EBIs had much more in common than different [36,40-42]. The intervention approach for this study is to focus on the common elements that many different interventions share, delivered by the most cost-efficient, scalable, and adaptable delivery strategies that permeate youths’ daily routines: mobile and social media technologies.

This hybrid implementation-effectiveness study examines alternative models for implementing the CDC’s guidelines for routine HIV/STI testing for YAHR of acquiring HIV and for delivering EBIs in modular elements instead of scripted manuals, while also monitoring implementation, costs, and effectiveness [43]. A randomized controlled trial (RCT) evaluates the efficacy and cost-effectiveness of the 4 intervention strategies of variable intensities and costs. This study aims to inform future prevention programs implemented by communities to avert the acquisition of HIV among young people by monitoring outcomes at 4-month intervals over 24 months.

## Methods

### Overview

All procedures in this study have been approved by the institutional review board (IRB) of the University of California, Los Angeles, which serves as the single IRB of Record for researchers at collaborating institutions. This is 1 of 3 studies in a National Institute of Child Health and Human Development (NICHD)-funded U19 Cooperative Agreement for the Adolescent (HIV Medicine) Trials Network (ATN) as well as a Management Core and Analytic Core [17,44-47]. This study began recruitment in May 2017. From June 2018 to December 2018, the protocol underwent a process of review and revision in collaboration with NICHD project scientists, the study’s scientific monitoring committee, and an external statistical expert, to meet budget constraints and align more closely with ATN scientific priorities. The major changes were (1) to reduce STI testing frequency from every 4 months routinely to only at baseline, 12, and 24 months and rectal testing only (unless requested by youth or indicated by symptoms); (2) stopping follow-up and intervention at 12 months with youth who are not MSM or transgender; and (3) changing randomization allocations for person-mediated intervention arms to have statistical power for MSM and transgender participants with 70% retention rates.

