### Design

Figure 1 shows the study design overview. The randomized controlled factorial design assesses efficacy of 3 intervention strategies (arms 1-3) and their combination (arm 4). The person-mediated interventions in arms 2 to 4 have a sample size of 270 per arm with 220 MSM and transgender youth, whereas the larger sample of 690 in the automated intervention only (arm 1) is because of the broader U19 Cooperative Agreement’s goal to identify youth acquiring HIV infection during follow-up to refer to a sister protocol on acute HIV infection [45], and earlier expectations to recruit youth that could be referred to other ATN protocols. Participants are followed longitudinally over 24 months (12 months for youth who are not MSM or transgender) and assessed at 4-month intervals by interviewers. Participants also complete a brief 7-question survey every week by text message (or email when nonresponsive to text messages). The overviews of assessments are provided below and described in detail in linked publications for the U19 [17,44-47].

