### Weekly Monitoring Surveys

The monitoring strategy is based on a weekly *Check-In* survey, which can be completed via text message or a Web link sent via email with a HIPAA–compliant RedCap version of the survey. Surveys assess the previous week time period with 7 questions on potential symptoms of acute HIV infection (yes/no), STI symptoms (yes/no), and number of days of feeling sad/depressed, sex without condoms, drug or alcohol use, not having a place to sleep or enough food; and miss taking medications (if taking medications). Participants receive a US $1 incentive per weekly survey completed, either in cash at their next 4-month follow-up assessment or on demand, including via electronic transfer (via Paypal, Venmo, or Zelle). Yes responses to HIV and STI symptom questions are reported to interviewers for follow-up risk assessment and rapid testing within 2 weeks. Reports on sadness/depression are monitored for potential follow-up and referral.

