### Outcome Measures

Our primary outcome is uptake and adherence to the HIV prevention continuum, according to the following measures, which will be analyzed individually and in sum (see Statistical Methods below):

Linkage to medical care reflected in a visit twice annually, at a minimum, to a health care providerConsistent utilization of condoms, PrEP, or PEPParticipation in other HIV prevention programs and servicesRepeat assessments for HIV and STI testing 3 times annually

Secondary outcomes include mental health symptoms, substance use, and housing security, which are hypothesized to impact primary outcomes as mediators or moderators of intervention effects.

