As a first step, MLM will be fit to each primary outcome and secondary outcome and intervention effects for each outcome will be evaluated separately. We will also evaluate the overall impact of the intervention across binary indicators for optimization of the prevention continuum utilizing a strategy employed by this team to analyze multiple outcomes with one overall statistic, to reflect if there is an overall impact on multiple binary outcomes [111]. Analysis of multiple outcomes through separate regressions increases the probability of finding a significant intervention effect by chance (ie, type I error is inflated). Therefore, we will properly adjust the type I error by conducting simulation studies to determine how many significant intervention effects are needed to declare an effective intervention. Simulation studies assume binary outcomes to be correlated to model a real-world phenomenon.

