### Strengths and Limitations

A limitation of this study is that study procedures and enhanced standard of care are relatively intensive interventions in and of themselves. Routine or indicated HIV and STI testing several times per year follows the CDC’s recommendations for people at high risk of acquiring HIV; however, this study operationalizes this with active and incentivized follow-up, community-based testing, and immediate treatment provision and partner therapy for STIs without a clinical visit. Daily text messaging and weekly monitoring with follow-up add another layer of intervention that cannot be directly assessed in this study. These limitations result from several factors, including utility for study assessments, ethical standards for research with vulnerable adolescents and the ATN to provide some base level of prevention support, goals for the broader U19 to identify youth with acute HIV infection from this study’s participants over time for a sister protocol [45], and to operationalize and examine costs and impacts of implementing CDC guidelines with community-based strategies [125]. Therefore, the potential efficacy and cost-effectiveness of the online peer support group and coaching interventions examined in this study should be considered within this context.

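### Routine STI testing was cut to once per follow-up year in 2018, but the primary testing measure still asks for HIV and STI testing three times a year, so its STI part changed meaning mid-trial

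*Protocol article*

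**What the plan says.** All places are in the Protocol article.

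- **Schedule in force.** Methods, Overview lists three major changes from the June to December 2018 review. The first was "to reduce STI testing frequency from every 4 months routinely to only at baseline, 12, and 24 months and rectal testing only", with the exception "unless requested by youth or indicated by symptoms". The third changed the randomization allocations for the person-mediated arms.
- **Primary measure.** Outcome Measures lists four measures of the prevention continuum, "which will be analyzed individually and in sum". The fourth is repeat HIV and STI testing three times a year. Textbox 1 in the Background gives the same frequency.
- **Visits.** Design keeps interviewer assessments every 4 months over 24 months ("12 months for youth who are not MSM or transgender"). The Overview lists no change to HIV testing frequency.
- **Symptom route.** Weekly Monitoring Surveys: "Yes responses to HIV and STI symptom questions are reported to interviewers for follow-up risk assessment and rapid testing within 2 weeks".
- **Overall analysis.** Aim 1 also plans to "evaluate the overall impact of the intervention across binary indicators for optimization of the prevention continuum".
- **Guideline.** The Background says that the CDC "recommends repeat and routine testing for HIV and sexually transmitted infection (STI) for YAHR every 3 or 6 months". The Abstract's Objective says that the study assessments implement the guideline for routine, repeat HIV and STI testing.

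**The concern.** Two current statements do not fit together. The outcome threshold matches the schedule that was withdrawn, not the one that replaced it.

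Under the earlier schedule, a participant who attended every visit met the STI part without doing anything else. On the plain reading of the current schedule, a participant with no symptoms and the same attendance falls short unless they ask for tests or obtain them elsewhere. One with symptoms may pass because symptom reports trigger testing. The same item therefore records different things before and after the revision.

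This matters for three reasons:

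- The measure names HIV and STI testing together. If it is scored as one item, an STI shortfall created by the schedule hides HIV testing that is unaffected.
- The item feeds both the summed outcome and the overall statistic.
- The arm proportions changed in the same revision. If the pass rate differs by schedule period and the arms are spread differently over the periods, part of any pooled arm difference reflects the period.

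**Working it through.** **Inputs.** Earlier STI schedule: every 4 months (Overview). Current STI schedule: months 0, 12 and 24 (Overview). Visits and HIV testing: every 4 months (Design). Required: 3 per year (Textbox 1, Outcome Measures). Follow-up: 24 months for MSM and transgender youth, 12 months for others (Design).

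**Step 1. Reproduce the plan's figure.** Earlier follow-up tests fall at months 4, 8, 12, 16, 20 and 24. Year 1, after month 0 up to month 12, has 3. Year 2, after month 12 up to month 24, has 3. This equals the stated three per year.

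**Step 2. Same count on the current schedule.** Year 1 has 1 (month 12) and year 2 has 1 (month 24). Counting each year from its opening visit instead (months 0 and 12) also gives 1 per year. The most that any 12-month window can hold, with both end visits counted, is 2.

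**Step 3. Shortfall of routine STI tests.**

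| | Required | Routine, follow-up only | Short by | Short by if baseline counts |
|---|---|---|---|---|
| To month 24 (MSM and transgender) | 6 | 2 | 6 − 2 = 4 | 6 − 3 = 3 |
| To month 12 (others) | 3 | 1 | 3 − 1 = 2 | 3 − 2 = 1 |
| Earlier schedule, to month 24 | 6 | 6 | 0 | 0 |
| HIV testing, to month 24 | 6 | 6 | 0 | 0 |

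**Step 4. Sensitivity to syphilis testing.** Rapid Diagnostic Tests lists syphilis as a separate fingerstick test, and Assessments says in general terms that the tests recur at follow-ups. The Overview cuts STI testing without exempting syphilis, but its limitation to rectal testing fits the swab tests better. If syphilis testing stayed 4-monthly and counts as STI testing, there are 3 per year and the shortfall is 0 for that test. It stays as in Step 3 for chlamydia and gonorrhea.

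**Step 5. Guideline interval.** The routine STI interval is now 12 months against 6 or 3 in the Background: 12/6 = 2 and 12/3 = 4 times as long.

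**Step 6. Overlap with the revision.** Recruitment ran about 13 months before the review began (May 2017 to June 2018) and was planned to run 5 to 8 months after it ended (December 2018 to June–August 2019). A participant enrolled in May 2017 reaches month 24 in May 2019, so one person's follow-up can span both schedules.

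**Step 7. How period can enter an arm comparison.** Let p₁ and p₂ be the pass rates on the STI part under the earlier and current schedules, the same in both arms (no intervention effect). Let f_A and f_B be the shares of two arms' scored intervals under the earlier schedule. The pooled difference is then

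(f_A − f_B) × (p₁ − p₂).

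It is zero only if the arms have the same mix of periods or the schedules give the same pass rate. The schedule change gives reason to expect p₁ ≠ p₂, and the allocation change gives reason to expect f_A ≠ f_B. The article gives neither the earlier allocation nor the date on which the change took effect, so no value can be put in.

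**The case against.** The strongest reply is that a supply schedule is not an outcome. The primary outcome is uptake by the youth, and nothing promises that the study provides every test. Testing on request remains, symptoms trigger testing, coaches link youth to services, and the questionnaires record health care use. A target above routine supply may even be the better endpoint. Under the earlier schedule, attending incentivised visits met it in every arm, which left little room for an intervention effect. Strengths and Limitations, with "Routine or indicated HIV and STI testing several times per year", also agrees with the exceptions in the Overview.

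Much of this stands:

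- A reader might infer that the STI part can no longer be met. The documents do not support that, since requested, symptom-triggered and possibly outside tests can reach three, and syphilis testing may have stayed 4-monthly.
- A reader might infer that symptom-triggered tests must be excluded as not being uptake. The article says no such thing, and Weekly Monitoring treats symptom monitoring as serving follow-up testing and linkage.
- Redefining the STI part as completion of the scheduled tests would turn it into attendance at months 12 and 24.
- Whether HIV and STI testing are scored jointly, and whether outside tests count, may be set in the full protocol or SAP.

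The reply does not remove the change of meaning. If attendance alone met the item before and does not now, the item measures something different in the two periods, whichever version is preferred.

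**Conclusion.** The point holds in this limited form and should be fixed. Routine study testing supplies 1 STI test per follow-up year (at most 2) against the 3 that the primary measure names. That leaves 2 per year (at least 1) to come from other sources. Only the superseded schedule met the figure by routine testing. HIV testing is unaffected, and one of four primary measures is involved, together with the summed outcome and the overall statistic.

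The counts rest on reading the Overview's cut as covering all STI tests; continued 4-monthly syphilis testing would narrow or remove the shortfall, depending on what counts. The spillover onto HIV testing assumes that the two are scored as one item.

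A reader might go further and infer that the trial is biased toward a particular arm. The documents do not support that: the stated schedule applies to all arms, and the size and direction of any bias cannot be derived. What they support is that schedule and allocation changed in one revision, so an unadjusted pooled comparison on this item is open to period confounding.

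**What to change.** 1. In Textbox 1 and Outcome Measures, make HIV testing (at least three times a year) and STI testing separate indicators.
2. State which STI tests count (routine, requested, symptom-triggered, outside, syphilis) and set an STI threshold that fits the current schedule.
3. When comparing arms on the STI indicator and on the summed outcome, adjust for or stratify by schedule period, before or after the revision. Since one person's follow-up can span both, assign the period to each scored interval.
4. Report results by reason for test as a sensitivity analysis, and do not exclude symptom-triggered tests from the main result.
5. In the Abstract's Objective, limit the claim of implementing the routine 3- or 6-month interval to HIV testing.

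**Cost.** No new visit or procedure is needed, but the reason for each STI test must be available in the data. It is a documented change to one primary component while data analysis is already under way (Results), so it should be dated and made without sight of results by arm. The trial also accepts a narrower claim about STI testing.
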